#### Sample size

Paramedics will recruit patients over a 6 month period. Based on data regarding throughput of sepsis cases in ED, we estimate a recruitment of approximately 100–150 patients. In this feasibility study, we will not be attempting to detect a clinically significant difference between the intervention and control groups in terms of outcomes, but rather to collect enough data to assess our methods against our progression criteria.

## Methods

### Usual care

At present, when a paramedic suspects a patient has sepsis, they will provide the patient with oxygen to maintain saturations over 94% (88% if the patient has chronic obstructive pulmonary disease) and give 250 ml boluses of 0.9% sodium chloride (up to 2000 ml if the patient is hypotensive, e.g. systolic blood pressure less than 100 mmHg, but clinical judgement can be used, taking into account the patient’s age and other clinical parameters). In addition, they will pre-alert the receiving hospital so that the patient can be taken directly to a resuscitation bay. During PhRASe, this care will continue to be given to both groups, with additional care given to patients in the intervention arm.

### Intervention development

A clinical intervention development group comprising paramedics, doctors, nurses, and pharmacists from prehospital care, emergency medicine, critical care, and microbiology met to define the exact treatment protocol and training methods for paramedics to follow early in the study period. They used clinical and local knowledge, research literature, and guidelines from the Joint Royal Colleges Ambulance Liaison Committee (JRCALC) and UHW. Based on advice from Public Health Wales, cefotaxime will be the antibiotic administered to patients in this feasibility study. The Screening Tool and Study Flowchart can be seen in Fig. 1; the screening tool is an adaptation of The UK Sepsis Trust’s Prehospital Sepsis Screening and Action Tool [17]. We decided only to include patients with Red Flag Sepsis in this feasibility study so that we did not broaden the use of antibiotics unnecessarily, in line with antimicrobial stewardship.

### Paramedic recruitment and training

We aim to recruit at least 60 of approximately 100 paramedics working in all ambulance stations and fire stations in the Cardiff and Vale of Glamorgan localities of WAST on a volunteer basis.

All study paramedics will be trained to recognise sepsis using the PhRASe screening tool, as well as to collect blood cultures and prepare and administer IV antibiotics. The training given to the paramedics will include the need to identify whether the patient has a known allergy to antibiotics, prior to administration, and the use of Aseptic Non Touch Technique (ANTT); although the collection of blood cultures within the hospital setting is routine, the collection of blood cultures in prehospital care is not a routinely practised skill for EMS staff and requires sound knowledge and practice of aseptic technique. The use of antibiotics (cefotaxime) will be supported by a patient group direction (PGD), which will allow the paramedics to administer a drug which is not routinely available to them under existing legal exemptions. Training will be delivered using formal group teaching sessions, e-learning, and one-to-one practical sessions.

### Randomisation

A randomisation schedule with a 1:1 ratio of ‘intervention’ or ‘control’ and stratified by paramedic will be produced by an independent statistician. Scratch cards will be produced to conceal the allocation, and a set of scratch cards will be issued to each study paramedic and be kept on their person in the pocket of their uniform during each working shift. When the study paramedic identifies an eligible patient, they will use their next sequential individually issued scratch card out of the sight of the patient. The unique number shown on the scratch card will become the patient’s study ID. This means the paramedic is always able to recruit a patient to the study and does not rely on having an Internet connection, a telephone signal, or a requirement to return to the ambulance to access the trial pack, to undertake the randomisation. The paramedic will retain the scratch card in order to store it with the randomisation log at the nurses’ station in UHW Resus, so that the PRSO can monitor randomisation.

### Blinding

Due to the nature of the intervention, the outcome of randomisation will not be blinded to the paramedics or patients. As data will be collected by the PRSO and handled by the data manager, they will also not be blinded to the allocation. The trial statistician will remain blinded to the allocation when conducting analysis.

### Outcomes

Part of the purpose of this study is to help us to define the primary outcome for a fully powered trial. Those to be tested include:Routinely collected anonymised dataMortalityLength of hospital stayPatient reported (at 90 days)Health-related quality of life using SF-12

Secondary outcomes to be tested include:

1. Routinely collected anonymised dataLength of intensive care unit stayTime from 999 call to administration of antibiotic by paramedic/in hospitalJob cycle time, on-scene timeHospital diagnosis of sepsis or other conditionIntervention costContamination of blood cultures

2. Patient reported (at 90 days)Patient satisfaction with care received by paramedics using quality of care monitor

### Data collection

#### Missed recruitments

There are two ways in which patients with sepsis who are attended by study paramedics may not be recruited:The study paramedic does not recognise that the patient has sepsisThe study paramedic recognises that the patient has sepsis but does not randomise them

As part of this feasibility study, we will monitor for missed recruitments so that we can determine whether paramedics are able to accurately recognise patients with sepsis, whether paramedics are compliant with the protocol, and how many patients could not be randomised due to the exclusion criteria. The PRSO will compare recruited patients to all the patients admitted to UHW by study paramedics with sepsis. The PRSO will be able to discuss with individual paramedics any problems or concerns that they may have.

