### Progression criteria

We will assess whether or not to proceed to a full multi-site RCT based on the following progression criteria, all of which should be met within reasonable limits (for example, if the progression criterion is within 5% of the target, we will review reasons for this and consider modifications to protocol; if within 10%, we will critically review reasons for this and assess whether major changes to protocol are likely to improve the issue; if more than 10%, we will not progress. The limits for each progression criterion will be stated in our statistical analysis plan; arbitrary limits of 5 and 10% have been suggested here for convenience).

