### Intervention feasibility

*Compliance with protocol by paramedics*—no less than 80% of patients recognised as eligible patients by study paramedics are randomised*Acceptability of intervention to patients*—mean patient satisfaction in intervention group is not less than 80% of patient satisfaction in the control group*Safety*—number of patients who experience adverse events has a difference of less than 10% between trial arms*Recognition of sepsis* (*success of training*)(a) At least 50% of patients with sepsis who are attended by study paramedics are recognised as eligible for the study.(b) At least 70% of randomised patients are diagnosed with sepsis in hospital.

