### Participants

#### Patient eligibility

Inclusion criteria:

• Adult patients (18 years or older) with ‘Red Flag’ Sepsis (as defined by the Screening Tool seen in Fig. 1)

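### The only described search for missed recruitments looks among sepsis admissions, which suits criterion 4(a) but biases the compliance rate in criterion 1 upward

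*Protocol article*

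**What the plan says.** Three parts of the protocol article bear on this point.

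- **Criterion 1** (Progression criteria, Intervention feasibility; compliance of paramedics with the protocol) requires that "no less than 80% of patients recognised as eligible patients by study paramedics are randomised". Eligibility is decided at the scene: under Patient eligibility, an adult "with ‘Red Flag’ Sepsis (as defined by the Screening Tool seen in Fig. 1"), attended by a study paramedic, to be conveyed to UHW, with neither exclusion. Hospital diagnosis plays no part in it.
- **Criterion 4**, in the same section, has two parts. Part (a) concerns the share of patients with sepsis whom study paramedics recognise as eligible. Part (b) reads "At least 70% of randomised patients are diagnosed with sepsis in hospital", so the plan accepts that up to 30% of randomised patients may turn out not to have sepsis.
- **Missed recruitments** (Data collection) opens with "There are two ways in which patients with sepsis who are attended by study paramedics may not be recruited": the paramedic does not recognise the sepsis, or recognises it but does not randomise. The monitoring is meant to show, besides recognition, "whether paramedics are compliant with the protocol, and how many patients could not be randomised due to the exclusion criteria". The procedure given is one comparison: "The PRSO will compare recruited patients to all the patients admitted to UHW by study paramedics with sepsis".

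The other recruitment record described is the randomisation log with retained scratch cards (Randomisation), and it is described for randomised patients. The review of the WAST Patient Clinical Record (Quantitative) is described for participants' demographics and treatment delivery.

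**The concern.** The monitoring is said to serve compliance, which is criterion 1, but it looks for misses in a population defined by sepsis and hospital admission. Criterion 1 is defined by paramedic recognition. The two populations differ by the patients who screen positive at the scene and prove not to have sepsis, a group that criterion 4(b) itself expects to exist.

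Such a patient counts in the numerator and denominator of criterion 1 if randomised, and in neither if not randomised. The loss falls only on non-randomised patients, so it can only raise the measured rate.

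At stake is one of nine progression criteria, and the randomisation rate on which recruitment to a full trial would be planned.

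**Working it through.** **Inputs**

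- Criterion 1 threshold: 80% (Intervention feasibility). This is a set threshold, so there is no derived figure to reproduce.
- Criterion 4(b) floor: 70% of randomised patients with hospital-diagnosed sepsis (same section).
- Expected recruitment: "we estimate a recruitment of approximately 100–150 patients" (Sample size).
- Illustrative bands (Progression criteria): within 5% of target, review; within 10%, critical review; beyond that, "if more than 10%, we will not progress". The article calls these limits arbitrary and leaves the final ones to the SAP.
- s, the share of recognised, non-randomised patients whom the sepsis-admission comparison finds: **not in the article, assumed**. The value 0.7 is borrowed from criterion 4(b), which is a minimum for randomised patients. The values 0.9 and 0.5 only show the range.

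**Step 1: who is counted among patients recognised as eligible**

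| Patient | Belongs in criterion 1 denominator | Found by a described route |
|---|---|---|
| Randomised, sepsis | yes | yes (randomisation log) |
| Randomised, no sepsis | yes | yes (randomisation log) |
| Not randomised, admitted with sepsis | yes | yes (comparison) |
| Not randomised, no sepsis | yes | no |

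**Step 2: formula**

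Let c be the true share randomised. Then

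measured = c / (c + s(1 − c)),

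which exceeds c whenever s < 1 and c < 1. Setting measured = 0.80 and solving gives

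c = 0.8s / (0.2 + 0.8s).

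**Step 3: what a measured 80% means**

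- s = 1: 0.80 / 1.00 = 80.0%, no bias.
- s = 0.9: 0.72 / 0.92 = 78.3%, which is 1.7 points short (review band).
- s = 0.7: 0.56 / 0.76 = 73.7%, which is 6.3 points short (critical-review band).
- s = 0.5: 0.40 / 0.60 = 66.7%, which is 13.3 points short (no-progress band).

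The article does not say whether its percentages are points or relative to the target. Relative to 80%, the shortfalls are 1.7/80 = 2.1%, 6.3/80 = 7.9% and 13.3/80 = 16.6%, so the bands are the same.

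In patients, with 100 randomised, 25 counted misses give 100/125 = 80%. The true misses would be 25/0.7 = 35.7 at s = 0.7, or 25/0.5 = 50 at s = 0.5. With 150 randomised, 37.5 counted misses stand for 53.6 or 75.

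**Step 4: the other direction**

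At s = 0.7, a true 75% is measured as 0.75 / (0.75 + 0.25 × 0.7) = 0.75 / 0.925 = 81.1%.

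**Step 5: does the result depend on the numerator?**

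Suppose both parts of the rate were restricted to patients with hospital sepsis. With a sepsis share of 0.7 in both groups, a true 80% stays 80%. With 0.7 among randomised and 0.5 among non-randomised patients, it reads (0.8 × 0.7) / (0.8 × 0.7 + 0.2 × 0.5) = 0.56 / 0.66 = 84.8%. That restricted rate is not criterion 1 as worded.

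**The case against.** **Other sources may exist.** This is a condensed article, and a screening log may sit in the full protocol. The PRSO collates routine call-out data, uses the Patient Clinical Record and talks to individual paramedics. This stands in part. A reader might infer that these patients are never counted, but the article supports only the narrower statement that no route it describes finds them. What remains is a stated method that does not fit its stated purpose, and a limit set in the SAP does not repair that.

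**The sentence on the comparison could be read differently.** The words about patients admitted with sepsis might mean patients brought in as suspected sepsis. This fails. The same comparison must reveal patients whose sepsis the paramedic did not recognise, so the sepsis cannot be the paramedic's own suspicion. Whether patients discharged from the ED fall outside the search is less clear, and the point does not need it.

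**The size is assumed.** This stands. Nothing in the article gives s for non-randomised patients. If non-randomisation came mainly from time pressure with plainly septic patients, s would be near 1 and the bias small. A reader might infer that paramedics hold back doubtful cases, which would lower s and also flatter criterion 4(b). The article offers no evidence of that, and the direction of bias does not depend on it.

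**The 80% mark is not a cliff.** This also stands. Under the illustrative bands a true 75% would lead to review, not a stop, so reading the 81.1% example as a failed trial passed off as a success goes too far.

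**A hospital-side check is independent of self-report.** True, and a reason to keep it for criterion 4(a) and to cross-check any paramedic log.

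**Conclusion.** The concern holds in limited form. The comparison with sepsis admissions matches criterion 4(a) and does not match criterion 1. Followed as written, with all randomised patients in the numerator as criterion 1 is worded, it biases measured compliance upward whenever any recognised, non-randomised patient proves not to have sepsis.

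The direction is firm and the size is not. Over the assumed range of s from 0.9 to 0.5, the overstatement at a measured 80% runs from 1.7 to 13.3 points. Under bands that the article itself calls arbitrary, that spans simple review to no progression. The conclusion rests on the article describing every route in use. If the full protocol holds a scene-side log of recognised but non-randomised patients, the point reduces to naming that log as the source for criterion 1.

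**What to change.** - **Criterion 1 denominator.** Take it from scene-side evidence that the paramedic recognised the patient: a completed positive screening tool, or suspected sepsis recorded in the WAST Patient Clinical Record, with no exclusion and conveyance to UHW. Count the patient regardless of hospital diagnosis or disposition. Do not widen this to every record that shows Red Flag signs, because that would bring in unrecognised patients, who belong to criterion 4(a).
- **Recording.** Have paramedics enter each recognised but non-randomised patient, with the reason, on the log already kept in UHW Resus. Have the PRSO cross-check it against the Patient Clinical Record, because self-report may be incomplete.
- **Existing comparison.** Keep the search of sepsis admissions for criterion 4(a), and say in the text that this is its use.

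The cost is a change of wording in the protocol and SAP, modest extra record review by the PRSO, and a compliance rate that may look less favourable. The log entries need to start with recruitment, since reasons for not randomising are hard to recover later.

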#### Quantitative

Data relating to clinical outcomes and hospital diagnosis will be obtained from the Secure Anonymised Information Linkage (SAIL) databank. The SF-12 and Quality of Care monitoring forms will be sent out to participants at 90 days (30 days for participants recruited in the last 2 months of the study) along with the Patient Dissent Forms to be returned directly to the research team at SU for data entry. Routine data will be used for paramedic call out information and will be collated by the PRSO. The PRSO will collect basic demographic details, i.e. age and gender, so that we can see whether participants’ baseline characteristics were similar between trial arms (indicating that randomisation was successful), as well as whether all patients who are allocated to intervention have both blood cultures taken and IV antibiotics given (as the paramedics may be unable to obtain blood cultures or give IV antibiotics in some cases). This information will be collected from patient’s WAST Patient Clinical Record.

#### Qualitative

Interview respondents will be sampled purposively [18] in a way previously used for Air Quality Alert scheme participants (findings not yet published). We will aim to explore with patients their experience of receiving the intervention and experience of recovery including overall quality of life. We will devise a semi-structured interview schedule, which will give the opportunity for patients to expand on information given on questionnaire forms about quality of life as well as asking for their views of the intervention through questions and prompts. We will sample 10 patients, selected purposively from those who receive IV antibiotics, to include a range of:AgeGenderTime and day of attendanceStudy paramedic who assessed the patient

Interviews will be conducted over the telephone, as this is felt to be the most convenient and least intrusive to respondents.

Approximately ten paramedics will be invited to participate in focus group(s) to explore their views on the intervention. We will devise a topic guide consisting of a series of questions and prompts about whether they consider prehospital IV antibiotics an acceptable method of providing treatment for patients with sepsis compared with usual treatment and their experience of delivering the intervention. The focus group(s) will be conducted towards the end of patient recruitment and will be recorded and transcribed. We will also collect any complaints to WAST or CVUHB relating to the trial, should any be received.

All qualitative data will be recorded (with explicit permission to do so) and transcribed verbatim.

### Data handling

Study data will be collected and managed using REDCap (Research Electronic Data Capture) electronic data capture tools hosted at SU; the PRSO and project administrator will input the data into REDCap [19]. REDCap is a secure, web-based application designed to support data capture for research studies, providing (1) an intuitive interface for validated data entry, (2) audit trails for tracking data manipulation and export procedures, (3) automated export procedures for seamless data downloads to common statistical packages, and (4) procedures for importing data from external sources.

Data will be monitored on an on-going basis for completeness and precision by the data manager and through source data verification; it will be frozen as soon as possible thereafter to prevent changes made in error. All reasonable effort will be made to minimise missing data, and we shall adopt a consistent approach to missing data at the analysis stage (except where individual variables require otherwise).

Identifiable information will be seen only by the qualitative researcher in SU in order to contact them to invite them to take part in an interview (if the patient has stated they are happy to be contacted for this purpose). Qualitative data will be anonymously stored on password-protected computers at SU. Identifiable information will be removed from interview transcripts and stored separately and securely.

The PRSO will hold identifiable data securely only to enable us to collect anonymised outcomes for them via SAIL.

### Analysis

The analysis of quantitative data will mainly be descriptive. We will report baseline characteristics, the number of participants randomised to each arm, and the number who received the treatment allocated. Continuous outcomes (e.g. SF-12 Score; length of stay) will be analysed using *t* tests, or non-parametric equivalents, and we will report mean and standard deviation, or median and interquartile range, along with 95% confidence intervals. Categorical outcomes (e.g. mortality, presence of sepsis) will be analysed using chi-squared tests, and we will report raw counts, proportions (*n*, %), and 95% confidence intervals. We will conduct exploratory analysis only of our potential primary outcomes to determine whether we have met progression criterion 8 (whether we remain in equipoise), as well as to help to decide which is the most appropriate for use as the primary outcome in a fully powered trial. We will report against each of our progression criteria to determine whether we should seek further funding for a fully powered trial and provide the necessary estimates for performing the power calculation for the potential fully powered trial, if warranted. We will perform analysis using SPSS and report results using the relevant CONSORT checklists [20, 21].

We will use a thematic analysis approach for the qualitative data, analysing the patient and paramedic datasets separately, with input from at least two members of the research team to each analysis. We will look for consistency of viewpoint among respondents and will explore any deviations from the predominant view and possible reasons for this.

As this is a feasibility study, no formal health economic analysis will be undertaken. Health economics will focus on establishing the main cost drivers by estimating the intervention implementation cost, necessary parameters required (including measures used to collect costs/outcomes), and suitable framework to undertake a full cost-effectiveness analysis in a future trial. We will examine the feasibility of collecting data on outcomes and resource use by examining the completeness and response rate from the measures and consider solutions to collecting data in a full trial. We will investigate the design options of a future economic evaluation required including capturing longer-term horizons, e.g. any modelling that would be required alongside a future in-trial analysis of cost-effectiveness.

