## Background

Sepsis is caused by the body’s dysregulated immune response to an infection. It is a time-critical condition which can rapidly lead to multi-organ failure and death [1, 2]. Sepsis has a mortality rate as high as 35%, killing between 36,000 and 64,000 people in the UK every year [3]. More people in the UK die from sepsis than lung cancer or breast and bowel cancer combined [4]. There is evidence to suggest that early diagnosis of sepsis and early administration of intravenous (IV) antibiotics can reduce morbidity and mortality from sepsis [4–6]. The prehospital phase of emergency medical care provides the earliest opportunity for identification of sepsis and delivery of immediate life-saving treatment for patients. It is known that recognition of sepsis in the ambulance can speed up care in the emergency department (ED) and that these patients get the required diagnostics and treatment sooner [7, 8]. Emergency medical services (EMS) personnel may, therefore, play a major role in the identification, pre-alert, and initial management of sepsis. Traditionally, EMS training has focused on assessing and managing ‘barn door’ presentations such as chest pain and ST segment elevation myocardial infarction, stroke and transient ischaemic attack, and acute trauma. To date there has been little focus on the acute assessment and management of sepsis, though the National Early Warning Score (NEWS) system is now used by some EMS providers. Approximately 50% of patients with sepsis in the ED arrive by ambulance [9, 10], with an average prehospital care time of 45 min [11]. This suggests an important window of opportunity for early recognition and care of sepsis before hospital arrival. Despite the importance of this condition and the need for rapid emergency care, the evidence base to support the use of prehospital antibiotics is weak [12, 13], with currently no well-defined prehospital protocol for sepsis in the UK. EMS personnel already play a key role in providing early recognition, initial treatment, and rapid transport for patients with other time-critical conditions; expanding the evidence base on the prehospital management of sepsis is crucial to determining whether earlier identification and management in the prehospital setting could improve health outcomes and speed up care at the ED.

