### RCT feasibility

5.*Acceptability of RCT to paramedics*—at least 60% of eligible paramedics agree to take part in the study6.*Acceptability of RCT to patients*—dissent to take part in the study is 30% or less7.*Retrieval of outcomes*—follow-up data for primary outcome suitable for fully powered trial can be collected for 70% or more of patients8.*Equipoise*—findings indicate that we remain in equipoise about the effectiveness of paramedic obtained blood cultures and prehospital antibiotics for sepsis.9.*Recruitment*—recruitment target met to at least 80%

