### Safety reporting

In the PhRASe feasibility study, safety reporting has two functions:

1. To monitor the safety of patients enrolled into the two arms of the trial;

2. To develop robust and practical safety reporting procedures for use in a fully powered multi-centred trial.

A principle of adverse event reporting is that safety should be monitored in both arms of the trial. Harms that occur after the patient has arrived at hospital could be a direct or indirect result of the treatment received in the prehospital environment. In some cases, we will be able to directly attribute the adverse event to the administration of antibiotics in the prehospital environment, but this will not be possible in all cases. We will monitor for the following serious adverse events (SAEs) in all patients up to 1 week:

• Anaphylaxis

• *C. difficile* infection

• Extravasation at the site administration of antibiotics

• Infection/cellulitis at the site of blood culture collection/administration of antibiotics

• Vascular damage at the site of blood culture collection/administration of antibiotics

SAE monitoring will be conducted by the PRSO so that the research team do not see any identifiable information. The PRSO will alert the Principal Investigator at UHW of all SAEs so that they can be assessed for seriousness and relatedness to the intervention. The Trial Manager will report any Suspected Unexpected Serious Adverse Reactions to the Research Ethics Committee, Sponsor, and the TSC’s Chair and Clinicians within 24 h of receiving notification of them. The rest of the TSC will be informed within 1 week, via the Chair.

We expect to capture harms beyond the 1-week follow-up period for SAEs through the outcomes for the trial, i.e. length of stay and mortality. Deaths and ICU admissions will be reported to the Trial Management Group on a three-monthly basis to ensure there are no safety concerns. For safety reporting purposes, this will be checked through routine records—this information will also be captured using the Secure Anonymised Information Linkage Databank, but due to a time lag in this information being available, we must also use alternative sources for interim reporting.

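### Length of stay and SF-12, two of the three candidate primary outcomes, are compared by plain two-group tests although death truncates both

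*Protocol article*

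**What the plan says.** The Outcomes section states the purpose: "Part of the purpose of this study is to help us to define the primary outcome for a fully powered trial". It lists three candidates: mortality, length of hospital stay, and SF-12 at 90 days.

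The Analysis section assigns the tests. The sentence that opens "Continuous outcomes (e.g. SF-12 Score; length of stay) will be analysed using" names the *t* test first. It then allows a rank-based fallback, with a matching choice of summary: "tests, or non-parametric equivalents, and we will report mean and standard deviation, or median and interquartile range". Mortality is handled apart: "Categorical outcomes (e.g. mortality, presence of sepsis) will be analysed using chi-squared tests".

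The same section gives the use of the results: "We will conduct exploratory analysis only of our potential primary outcomes to determine whether we have met progression criterion 8", which concerns equipoise. They also help choose the future primary outcome, and the study is to supply the estimates for the full trial's power calculation. Safety reporting adds a further use: "We expect to capture harms beyond the 1-week follow-up period for SAEs through the outcomes for the trial, i.e. length of stay and mortality".

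The Consent section keeps deceased patients in the analysis. It also has vital status checked before the questionnaire goes out, so a patient who has died by then has no SF-12. The Background gives the only mortality figure: "Sepsis has a mortality rate as high as 35" per cent.

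**The concern.** A hospital stay can end in discharge or in death. A test on all patients' stays treats the two endings alike, so a patient who dies on day 2 contributes a more favourable value than one who goes home on day 10. If the intervention saves lives and deaths come early, it converts short stays into longer ones and appears to cost bed days. Since stay is also to be read as a late harm signal, a survival gain could be taken for harm.

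SF-12 has a different problem. After death it is undefined rather than missing, so a general approach to missing data does not settle it. The comparison is between the survivors of each arm, and survival may itself depend on the arm. Patients kept alive by the intervention may be frailer than those who would have lived anyway, and they then lower the intervention mean.

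At stake are the equipoise judgement (criterion 8), the choice of primary outcome, and the variance carried into the full trial's power calculation.

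**Working it through.** The plan states no effect size, standard deviation or power, so it has no figure of its own to reproduce. Inputs from the protocol are mortality of up to 35% (Background), 100–150 patients (Sample size) and 1:1 allocation (Design), hence 50–75 per arm. Assumed inputs are intervention-arm mortality of 25%, the mean stays of survivors (S) and of patients who die (D), and the SF-12 means.

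**1. Mean stay over all patients** = (1 − m) × S + m × D, where m is mortality.

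With S = 12 and D = 5 in both arms:
- at 35% mortality: 0.65 × 12 + 0.35 × 5 = 9.55 days
- at 25% mortality: 0.75 × 12 + 0.25 × 5 = 10.25 days

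The arm with fewer deaths is 0.70 day longer, although survivors' stays are identical.

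**2. Range over D.** With S = 10, the difference (intervention minus control) is 0.10 × (10 − D). In 3,000 simulated trials per row (gamma stays in survivors, exponential in deaths), the arm with fewer deaths looked worse as often as shown:

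| D (days) | Difference in mean stay | Longer mean, N = 100 / 150 | Higher mean rank, N = 100 / 150 |
|---|---|---|---|
| 3 | +0.7 | 71% / 72% | 74% / 77% |
| 5 | +0.5 | 64% / 67% | 67% / 70% |
| 10 | 0 | 48% / 50% | 51% / 56% |
| 14 | −0.4 | 42% / 40% | 45% / 45% |

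The ranks point the wrong way at least as often as the means, so the non-parametric option is no remedy. A significant t test in the wrong direction was uncommon: 7–10% of trials at D = 3 and 5–7% at D = 5.

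**3. Does the separate mortality test guard against this?** For 35% versus 25%, two-sided 5%, power = Φ[(0.10 − 1.96 × √(2 × 0.30 × 0.70 / n)) / √((0.35 × 0.65 + 0.25 × 0.75) / n)].
- n = 50 per arm: (0.100 − 0.180) / 0.0911 = −0.87, power 19%
- n = 75 per arm: (0.100 − 0.147) / 0.0744 = −0.63, power 27%

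The mortality test is unlikely to show why stay lengthened.

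**4. SF-12 in survivors.** The largest share of patients who can have a score is 1 − m: 65% at 35% mortality, 80% at 20% and 90% at 10%. Suppose patients who would survive in either arm average 42 and the extra 10% who survive only with the intervention average L. The intervention survivors' mean is (0.65 × 42 + 0.10 × L) / 0.75.
- L = 30: 40.40, a fall of 1.6 points
- L = 35: 41.07, a fall of 0.9
- L = 40: 41.73, a fall of 0.3

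No patient has been harmed in any of these cases.

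**5. SF-12 against criterion 7**, which asks that "follow-up data for primary outcome suitable for fully powered trial can be collected for 70% or more of patients". If deaths stay in the denominator, SF-12 cannot reach 70% once mortality exceeds 30%. At 20% mortality it needs 0.70 / 0.80 = 87.5% of survivors to respond. If deaths were instead counted as retrieved, then at 35% mortality the criterion would be met with (0.70 − 0.35) / 0.65 = 54% of survivors responding. Each single denominator misleads in its own way.

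**6. Days alive and out of hospital to day 90**, 0 for deaths, with S = 12: 0.65 × 78 = 50.7 days versus 0.75 × 78 = 58.5 days. The direction now agrees with the survival benefit.

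**The case against.** The strongest reply is that this is detail for the statistical analysis plan, which the protocol mentions and which is not shown. That stands in part, since a rule for deaths may be there. But the article does name the tests and the uses of their results, and what it names does not suit these two outcomes.

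Several stronger readings are tempting, and the documents do not support them.
- *That the plan ignores death.* Mortality is a candidate primary outcome with its own test, vital status is checked before mailing, deceased patients are retained, and deaths are reported to the Trial Management Group every three months.
- *That only t tests are planned.* Rank-based alternatives with medians are allowed, although they do not help here.
- *That a third of patients will have no SF-12.* The 35% is a background ceiling without a time horizon, not a planning figure. In addition, patients recruited in the last two months are surveyed at 30 days.
- *That stay will have the wrong sign.* That needs deaths to come sooner than discharges, which the protocol does not say. A longer all-patient stay would also be a true difference in bed use; the error lies in reading it as harm.
- *That poor SF-12 retrieval fails criterion 7.* The criterion concerns whichever outcome suits the full trial, and mortality and stay come from routine data. Finding SF-12 hard to obtain is a proper feasibility result.

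It is also fair that the comparisons are exploratory, that criterion 8 carries no stated significance rule, and that the gain in days alive and out of hospital above (0.10 × 78 = 7.8 days) is largely the assumed mortality difference in another unit.

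**Conclusion.** The point holds at moderate severity. Followed as written, the plan gives a stay comparison mixed with mortality and a survivor-only SF-12 comparison. These inform the equipoise judgement, the choice of primary outcome and the power calculation, and stay also serves as a signal of late harm.

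Under assumed mortality of 35% versus 25%, the distortion in mean stay runs from +0.7 day (S = 12 and D = 5, or S = 10 and D = 3) through nil (equal means) to −0.4 day (S = 10 and D = 14). The survivors' SF-12 mean could fall by 0.3–1.6 points without harm. All stays, SF-12 means and the 25% are assumptions; only the 35% ceiling and the sample size come from the protocol. The flaw does not depend on the direction of the bias: a difference in raw stay cannot be read as benefit or harm without knowing how each stay ended.

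**What to change.** Before these results inform criterion 8, the choice of primary outcome or the power calculation:
- Use days alive and out of hospital to day 90 (0 for patients who die) from the linked data as the candidate outcome in place of all-patient raw stay. The Abstract gives 90 days for linked follow-up; if late recruits have less, use one common shorter horizon for all.
- Show raw length of stay separately for survivors and for patients who die, by arm.
- Report SF-12 descriptively in survivors, with a supplementary rank comparison that places deaths lowest.
- When judging SF-12 against criterion 7, report retrieval both among all randomised patients and among survivors. Do not count deaths as retrieved questionnaires.

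The cost is a few derived variables, some wording and a little extra analysis, with no new data collection. The downside is a composite that is less familiar than raw stay and, where mortality is high, driven largely by deaths. It should therefore be shown beside mortality and raw stay by vital status.
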